## Abstract

**Background:**

Cancer survivors have to deal with a wide range of physical symptoms, psychological, social and existential concerns, and lifestyle issues related to cancer and its treatment. Therefore, it is essential that they have access to optimal supportive care services. The eHealth self-management application Oncokompas was developed to support cancer survivors with where they need to turn to for advice and guidance, as well as to increase their knowledge on the availability of optimal support. A randomised controlled trial will be conducted to assess the efficacy, cost-utility and reach of Oncokompas as an eHealth self-management application compared with care as usual among cancer survivors.

**Methods/design:**

Adult cancer survivors diagnosed with breast, colorectal or head and neck cancer or lymphoma who are at 3 months to 5 years since curative treatment will be included. In total, 544 cancer survivors will be randomly assigned to the intervention group or a wait-list control group. The primary outcome measure is patient activation. Secondary outcome measures include self-efficacy, personal control, perceived patient-physician interaction, need for supportive care, mental adjustment to cancer and health-related quality of life. Furthermore, cost-utility outcomes will be assessed. *Reach* is defined as the percentage of cancer survivors who get access to Oncokompas within the context of this trial. Questionnaires will be administered at baseline, post-intervention and at 3- and 6-month follow-up.

**Discussion:**

In this study, we will evaluate the efficacy and cost-utility of Oncokompas among cancer survivors, as well as the reach of Oncokompas. These are essential first steps in the translation of research into practice and contribute to sustainable adoption, implementation and maintenance of an evidence-based Oncokompas.

**Trial registration:**

Netherlands Trial Register identifier: NTR5774. Registered on 8 March 2016.

**Electronic supplementary material:**

The online version of this article (doi:10.1186/s13063-017-1952-1) contains supplementary material, which is available to authorized users.

## Background

Cancer survivors have to deal with a wide range of physical symptoms, psychological, social and existential concerns, and lifestyle issues related to their cancer and its treatment. These problems can negatively affect health-related quality of life (HRQOL), may interfere with return to work and often result in higher medical care use [1, 2]. Therefore, it is essential that cancer survivors have access to optimal supportive care services. Supportive care for cancer survivors includes management of physical and psychological symptoms, social functioning, and existential and lifestyle issues related to cancer recurrence. Supportive care (e.g., physiotherapy, psychological support, support in the relationship with partner or children, support with existential questions or self-help interventions targeting a healthy lifestyle) is increasingly recognised as an integral part of quality cancer treatment [1, 2]. Although there is evidence that supportive care is effective [3–5], referral rates are low, and many cancer survivors have unmet needs [6, 7] related to, for example, fatigue, anxiety, depression or sexuality issues.

To improve accessibility to optimal supportive care services, cancer survivors are expected to adopt an active role in managing their own care [8]. Several studies have shown that self-management strategies ranging from educational interventions, exercise programs and (online) self-help interventions targeting psychological distress are beneficial for cancer survivors in terms of patient activation and self-efficacy [9–11]. Patient activation can be described as an individual’s knowledge, skill, and confidence for managing their health and healthcare [12]. Less activated people are more likely than highly activated patients to have unmet medical needs and to delay seeking medical care. As patients’ activation levels increase, they gain a greater sense of control over their health and feel empowered to take action [13].

There is growing interest in eHealth among patients, healthcare providers, healthcare assurance companies and policy-makers as a means to improve self-management [1]. To support cancer survivors in where they need to turn for advice and guidance, as well as increasing their knowledge on optimal support, the eHealth self-management application Oncokompas was developed. With Oncokompas, cancer survivors can monitor their quality of life by means of Patient-Reported Outcome Measures (PROMs), which is followed by automatically generated tailored feedback and personalised advice on supportive care services [14].

To ensure sustainable usage of Oncokompas, participatory design principles were followed [15], meaning that cancer survivors and healthcare professionals (HCPs) were involved in each step of the development process [14, 16, 17]. This approach resulted in an eHealth application which fits the needs of patients and HCPs. *See* the Methods section for more information on Oncokompas and its development process. The aim of the present study is to assess the efficacy and cost-utility of Oncokompas as an eHealth self-management application among cancer survivors, as well as the reach of Oncokompas within the context of this trial.

## Methods/design

This study is a randomised controlled trial (RCT) evaluating the efficacy and cost-utility of the eHealth application Oncokompas among cancer survivors, as well as the reach of Oncokompas. We closely followed the Standard Protocol Items: Recommendations for Interventional Trials (SPIRIT) checklist [18, 19] (*see* Additional file 1). Cancer survivors will be randomised into the intervention group (whose members will obtain access to the intervention) or a wait-list control group (whose members will obtain access to the intervention after a 6-month waiting period). The study is subdivided into two parts: part 1 concerns the reach and part 2 the efficacy and cost-utility of Oncokompas. The first part comprises the baseline assessment, and the second part comprises the post-intervention and follow-up assessments.

### Intervention

Oncokompas is an eHealth self-management application that supports cancer survivors in finding and obtaining optimal supportive care, adjusted to their personal health status and preferences. Oncokompas consists of three components: ‘Measure’, ‘Learn’, and ‘Act’. In the Measure component, cancer survivors can independently complete PROMs targeting the following quality-of-life domains: physical, psychological and social functioning, healthy lifestyle, and existential issues. Tumour-specific modules are available for patients with breast cancer, colorectal cancer, head and neck cancer, and lymphoma. Specific PROMs were selected by the project team in collaboration with teams of experts and on the basis of Dutch practical guidelines (from the Netherlands Comprehensive Cancer Organisation [IKNL]) and literature searches. Data derived from the Measure component are processed in real time and linked to tailored feedback to the cancer survivor in the Learn component. All algorithm calculations are based on available cut-off scores or are defined on the basis of Dutch practice guidelines, literature searches and/or consensus of teams of experts. In the Learn component, feedback is provided to the participant on the level of topics (e.g., depression, fatigue) by means of a three-color system: green (no elevated well-being risks), orange (elevated well-being risks) and red (seriously elevated well-being risks). Cancer survivors receive personalised information on the outcomes; for example, on the topic of depression, information is provided on the symptoms of depression and the proportion of cancer survivors who experience depressive symptoms. Special attention is paid to evidence-based associations between outcomes. For example, feedback on the association between depression and fatigue is provided if a participant has an orange or a red score on depression as well as fatigue. The feedback in the Learn component concludes with comprehensive self-care advice with tips and tools. All of this advice is tailored to the individual cancer survivor. In the Act component, cancer survivors are provided with personalised supportive care options based on their PROM scores and expressed preferences (e.g., preference for individual therapy versus group therapy). If a participant has elevated well-being risks (orange score), the feedback includes suggestions for self-help interventions. If a participant has seriously elevated well-being risks, the feedback includes advice to contact the participant’s own medical specialist or general practitioner [14, 17].

Several studies were conducted to optimally fit Oncokompas to patients’ and care providers’ preferences. Cancer survivors and HCPs were involved in each step of the development process. A needs assessment was conducted among cancer survivors and HCPs (step 1) [16]. Usability was tested by cancer survivors in two iterative cycles, and HCPs participated in cognitive walk-throughs (step 2) [17]. Cancer survivors participated in a multi-centre pilot study to assess feasibility (step 3) [14]. Oncokompas was optimised on the basis of the feasibility testing results.

### Study population

#### Part 1: inclusion and exclusion criteria

Inclusion criteria are cancer survivors diagnosed with breast, colorectal, or head and neck cancer or lymphoma; being aged ≥18 years (no upper limit); and having finished treatment with curative intent for 3 months to 5 years (all treatment modalities). Cancer survivors who have not yet completed endocrine therapy or immunotherapy for their breast cancer will be included 3 months to 5 years after their primary treatment. Exclusion criteria are male cancer survivors diagnosed with breast cancer and/or individuals with severe cognitive impairment, insufficient mastery of the Dutch language, and physical inability to complete a questionnaire.

#### Part 2: additional exclusion criterion

In addition to the inclusion and exclusion criteria of part 1, participants are excluded for part 2 if they do not have access to the Internet, do not use the Internet or do not have access to an email address.

### Study design

The study is introduced to eligible cancer survivors as a baseline study (part 1) and a follow-up study (part 2). Study information is given and informed consent is requested for both parts separately. Cancer survivors who fulfil the inclusion criteria and not the exclusion criteria for the first part are asked to participate in the baseline study. Baseline assessment (T0) will take place after the first informed consent form is signed. After completion of the baseline assessment, participants who fulfil the inclusion criteria and not the exclusion criteria for the second part are asked to participate in the follow-up study. After the second informed consent is given, participants will be randomly allocated to one of the two study arms. Follow-up assessments will take place post-intervention (T1) and at 3-month (T2) and 6-month (T3) follow-up. In the intervention group, T1 assessment takes place 1 week after completion of Oncokompas or 2 weeks after inclusion when Oncokompas is not completed. In the control group, T1 assessment takes place 2 weeks after inclusion. Participants allocated to the control group obtain access to Oncokompas after completion of the T3 assessment. A flowchart of the RCT is shown in Fig. 1, and the schedule of enrolment, interventions and assessments (according to SPIRIT guidelines) is provided in Fig. 2.

**Fig. 1 Fig1:**
[figure not shown]
Flowchart of the randomised controlled trial

**Fig. 2 Fig2:**
[figure not shown]
Standard Protocol Items: Recommendations for Interventional Trials (SPIRIT) schedule of enrolment, interventions and assessments

### Inclusion procedures

We will recruit cancer survivors through the Netherlands Cancer Registry (NCR), which is hosted by the IKNL. The NCR registers all newly diagnosed cancer patients within 6 months after diagnosis. Data collection will be performed using the registry of Patient Reported Outcomes Following Initial treatment and Long term Evaluation of Survivorship (PROFILES). PROFILES is a registry for the study of the physical and psychosocial impact of cancer and its treatment using a dynamic, growing, population-based cohort of both short- and long-term cancer survivors. PROFILES contains a large web-based component and is linked directly to clinical data from the NCR [20].

#### Part 1

A random sample of 1088 cancer survivors will be drawn from the NCR. This number is based on a power calculation (*see* ‘Sample size’ subheading) and an expected drop-out rate of 50% between parts 1 and 2. The selection of patients will be stratified by tumour type (breast, colorectal, and head and neck cancer or lymphoma) and time after finishing treatment (<6 months, 6–12 months, 12–24 months or 24–60 months after treatment). After excluding recently deceased patients, the (former) treating physicians are asked to verify the patients’ study eligibility (e.g., excluding patients with serious cognitive impairment or who are in transition to terminal care). Cancer survivors are invited to participate in the baseline study via a letter from their (former) treating physician. The letter includes a link to a secure website as well as a login name and password. Interested cancer survivors can log in and provide informed consent for the first part of the study and complete the baseline questionnaire. If a cancer survivor does not have access to Internet or prefers written rather than digital communication, an informed consent form and a paper-and-pencil questionnaire are sent by postal mail. Non-respondents will be sent a reminder letter and a paper-and-pencil questionnaire within 4 weeks. If they do not respond to this reminder, they will be contacted by telephone within 2 weeks.

#### Part 2

Cancer survivors who complete the baseline questionnaire will be invited to participate in the follow-up study. An email with information about the follow-up study and Oncokompas will be sent. Interested cancer survivors can provide informed consent for the second part of the study and complete the follow-up questionnaires on the same secure website where the baseline questionnaire resides. Cancer survivors who are not interested in participating in the study are asked about their reasons for non-participation. Non-respondents will be sent a reminder by email within 2 weeks. If they do not respond to this reminder, they will be contacted by telephone within 2 weeks.

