### Sample size

To demonstrate presence of an effect between T3 and T0 of at least 0.5 standard units as statistically significant in a one-tailed test at α = 0.05 and a power of (1 − β) = 0.80, a minimum of 51 participants per arm in each condition will be required at follow-up. Anticipating a drop-out rate of 25% between T0 and T3, 68 participants per condition arm per tumour type need to be included at T0. The total study cohort thus comprises 544 cancer survivors representing 136 cancer survivors per tumour type (breast, colorectal, and head and neck cancer or lymphoma).

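### The 1088 to be drawn from the registry is really the number of baseline completers needed; losses between the draw and baseline are not counted

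*Protocol article*

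**What the plan says.** The Sample size section sets 51 evaluable participants per arm, allows 25% drop-out, and concludes that "68 participants per condition arm per tumour type need to be included at T0", giving 136 per tumour type and 544 in all.

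The Inclusion procedures, Part 1, turn this into a recruitment number: "A random sample of 1088 cancer survivors will be drawn from the NCR". The stated basis is the power calculation and "an expected drop-out rate of 50% between parts 1 and 2".

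Methods/design defines the two parts: "The first part comprises the baseline assessment, and the second part comprises the post-intervention and follow-up assessments". Under Inclusion procedures, Part 2, only people who have completed the baseline questionnaire are invited to the follow-up study; the second consent and randomisation come after that.

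The Part 1 text also lists what happens between the draw and baseline. "After excluding recently deceased patients, the (former) treating physicians are asked to verify the patients’ study eligibility". Those who remain are invited by letter, and non-response is expected: "Non-respondents will be sent a reminder letter and a paper-and-pencil questionnaire within 4 weeks", followed by a telephone call. No rate is given for any of these losses, and no further draw is described.

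**The concern.** The 50% loss starts at baseline completion and ends at consent to the randomised part. Dividing 544 by 0.50 therefore gives the number who must complete baseline. The article attaches that number to an earlier step, the registry draw. For a single draw of 1088 to give 544 randomised, everyone drawn would have to be alive, eligible and willing to complete the questionnaire. Yet the same section provides for people who are not.

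At stake are the 544 to be randomised and the 80% power, which the Sample size section sets within each tumour type. The reach result is also affected: if more people are drawn later without a stated rule, its denominator changes.

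**Working it through.** **Inputs from the article.** Effect 0.5 SD, one-tailed α = 0.05, power 0.80, 51 evaluable per arm, 25% drop-out to T3, two arms, four tumour types (544/136), 50% loss between parts 1 and 2.

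**Reproducing the plan's figures.**
- Power for a one-sided two-sample t test with n per arm is the probability that a noncentral t variable, with 2n − 2 degrees of freedom and noncentrality 0.5 × √(n/2), exceeds the 95th percentile of the central t. The smallest n giving at least 0.80 is 51 (power 0.806), as stated.
- 51/0.75 = 68 per arm per tumour type.
- 68 × 2 × 4 = 544.
- 544/(1 − 0.50) = 1088.

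Every figure reproduces. The 50% loss alone accounts for the whole step from 544 to 1088, which leaves nothing for losses before baseline.

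**Adding the missing step.** Let r be the share of those drawn who complete baseline, that is, the eligible fraction times the response fraction. The article gives no value, so the values of r below are assumptions.
- Randomised from one draw: 1088 × r × 0.50.
- Evaluable per arm per tumour type: randomised/8 × 0.75.
- Evaluable per arm pooled over tumour types: randomised/2 × 0.75.
- Draw needed for 544 randomised: 1088/r, rounded up.

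| r (assumed) | Randomised | Evaluable per arm per tumour type | One-sided power per tumour type | One-sided power, pooled | Draw needed |
|---|---|---|---|---|---|
| 1.0 | 544 | 51.0 | 0.81 | >0.99 | 1088 |
| 0.9 | 490 | 45.9 | 0.77 | >0.99 | 1209 |
| 0.7 | 381 | 35.7 | 0.67 | >0.99 | 1555 |
| 0.5 | 272 | 25.5 | 0.55 | 0.97 | 2176 |

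Each 10% of the draw lost before baseline costs 1088 × 0.10 × 0.50 ≈ 54 randomised participants.

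**The case against.** **The 50% may loosely cover everything from the draw to the second consent.** The draw, eligibility check and invitation all stand under the Part 1 heading, so this reading is possible, and 1088 would then give 544. It does not match the wording, which places the loss between the two parts and defines the first part as the baseline assessment. It would also be demanding: r times the part 2 uptake would have to equal 0.50. With r = 0.7, uptake among baseline completers would have to be 0.50/0.7 = 0.71; with r = 0.5, it would have to be 100%, although people without Internet or email are also excluded at that step. If this reading was meant, the sentence still needs correcting.

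**A reader might infer that the trial cannot reach 544.** The article does not support that. Nothing makes 1088 a ceiling or rules out further draws, inclusion was ongoing at publication, and the flowchart, which is not shown, may give counts by step. What stands is that a single draw of 1088, as described, falls short.

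**A reader might infer that the trial as a whole loses its power.** It does not. The loss is within tumour type. The efficacy analysis is described as a comparison of the two groups over time, and pooled over tumour types its power at 0.5 SD stays above 0.95 (one-sided) across the range shown. The per-tumour-type loss still counts, because that is how the article sizes the trial.

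**A reader might infer an implied reach of 50% of everyone drawn.** The Reach section uses eligible, invited survivors as the denominator, so deceased and ineligible people are outside it.

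**A reader might see a second numerical error in the reference to T0.** T0 does precede randomisation, but a number given per arm can only mean randomised participants. This is loose wording.

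**Conclusion.** The concern holds as a misplaced number. The arithmetic is right, but 1088 belongs to baseline completion and is stated as the registry draw. Any loss between the draw and baseline takes a single draw of 1088 below 544 randomised. The direction of the error follows from the article alone; its size rests on the assumed share completing baseline. Over an assumed 90% to 50%, between 490 and 272 would be randomised, and one-sided power per tumour type would be about 0.77 to 0.55 instead of 0.80. These figures keep the article's own 50% and 25% losses and spread the shortfall evenly over arms and tumour types. The pooled comparison is not in danger at the planned effect.

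**What to change.** - In Inclusion procedures, Part 1, restate 1088 as the required number of baseline completers, 272 per tumour type (1088/4).
- Give the registry draw as 1088 divided by the assumed eligible fraction and the assumed response fraction, with both values stated. Alternatively, state that random registry batches continue within each stratum until 136 per tumour type are randomised.
- Keep all eligible invited survivors from every batch in the reach denominator, as the Reach section defines it.
- If no further draw is made, restate the expected number randomised and the resulting power per tumour type.
- As a minor wording correction in the Sample size section, describe the 68 per arm per tumour type as randomised instead of included at T0.

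The cost is a larger draw and more invitation letters: for example, 1555 drawn instead of 1088 if 70% complete baseline. The 544 to be randomised and the analysis stay as they are.

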### Randomisation

Cancer survivors who meet the inclusion criteria and give informed consent for the second part of the study are randomly allocated in a 1:1 ratio to either the intervention group (access to Oncokompas) or the wait-list control group (access to Oncokompas after a 6-month waiting period). Randomisation to either the intervention or the control group will be performed by a researcher not involved in the study using block randomisation. The blocks will have a length of 68. The researcher will determine all possible balanced combinations of assignment within the block (i.e., equal number for all groups within the block). Randomisation will be stratified by tumour type (breast, colorectal, and head and neck cancer or lymphoma). It is expected that this variable has prognostic relevance and therefore needs to be distributed evenly across both groups. The allocation sequence will be generated by PROFILES and will be made available by a data download from the PROFILES database. The researcher ([name]) will assign participants either to the intervention group and invite participants to engage with Oncokompas by email or to the control group and place participants on the waiting list, where the participants’ email address is blocked from Oncokompas for 6 months.

